### Setting

The intervention is implemented in Mehsana district, located in Western India in the state of Gujarat. It is primarily a rural district (75% rural), with a rural population of 1.52 million people, of which approximately one million are above 18 years of age. The district is divided into 10 blocks/ sub-districts with a total of 645 villages and 316,536 rural households [16]. Almost half (45.4%) of Mehsana’s rural population has a low standard of living as defined by the Standard of Living Index [17]. Most residents (53%) are employed in the agricultural sector. The rural population of the Mehsana district is economically disadvantaged as agriculture is not always a viable occupation given uncertain climatic events [16]. In terms of health services, Mehsana has 56 PHCs, 11 Community Health Centers and 1 District Hospital staffed by 2 psychiatrists, along with District Mental Health Program (DMHP) which provides additional human resources (such as a psychologist and social worker) for mental health at the community level. Mental health care is primarily delivered by psychiatrists at the District Hospital and the psychiatrists also visit Community Health Centers on a fortnightly basis in rotation, as part of DMHP. The district hospital has in-patient and out-patient services for persons with mental illness, and limited psychosocial support services.

### Participants

The study sample consists of adult community members with CMD (e.g. anxiety and depression) residing in rural villages in the Mehsana district.

#### Inclusion Criteria

▪ Persons aged 18 years or more and less than 65 years of age▪ A Score of 3 or above on the General Health Questionnaire (GHQ-12), indicating a case with CMD

#### Exclusion criteria

▪ Persons who cannot provide informed consent or decline participation in the study▪ Persons with a terminal medical condition▪ Persons who have suicidal ideation or plans for suicide at the baseline interview

### Primary outcome

The primary outcome is the symptomatic improvement of CMD as measured using a validated Gujarati version of the GHQ-12 [18] from baseline to 3-month and 8-month follow-up to evaluate sustained effects of the intervention. The GHQ-12 is a widely used screening tool with reliable sensitivity for assessing CMD [19]. GHQ-12 is a dichotomous 12-item questionnaire with each item rated on a 4-point scale, with possible responses being “less than usual,” “no more than usual,” “rather more than usual,” or “much more than usual.” We used a bimodal scoring method, whereby “less than usual” and “no more than usual” is scored as 0 point, and “rather more than usual” and “much more than usual” is scored as 1 [18]. GHQ-12 scores will be analyzed as both continuous (ranging from 0 to 12) and categorical outcomes (case defined as 3 and above scores on GHQ scale; non-case as less than 3 scores on GHQ scale).

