**Methods:**

The impact of the *Atmiyata* intervention is evaluated through a stepped wedge cluster randomized controlled trial (SW-CRCT) with a nested economic evaluation. The trial is implemented across 10 sub-blocks (645 villages) in Mehsana district in the state of Gujarat, with a catchment area of 1.52 million rural adults. There are 56 primary health centers (PHCs) in Mehsana district and villages covered under these PHCs are equally divided into four groups of clusters of 14 PHCs each. The intervention is rolled out in a staggered manner in these groups of villages at an interval of 5 months.

The primary outcome is symptomatic improvement measured through the GHQ-12 at a 3-month follow-up. Secondary outcomes include: quality of life using the EURO-QoL (EQ- 5D), symptom improvement measured by the Self-Reporting Questionnaire-20 (SRQ-20), functioning using the World Health Organization’s Disability Assessment Scale (WHO-DAS-12), depression symptoms using the Patient Health Questionnaire (PHQ-9), anxiety symptoms using Generalized Anxiety Disorder Questionnaire (GAD-7), and social participation using the Social Participation Scale (SPS). Generalized linear mixed effects model is employed for binary outcomes and linear mixed effects model for continuous outcomes. A Return on Investment (ROI) analysis of the intervention will be conducted to understand whether the intervention generates any return on financial investments made into the project.

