### Secondary outcomes

Secondary outcome measures are assessed at 3 and 8 months after the start of the intervention (Table 1).

**Table 1 Tab1:** Follow-up assessment of tools with time points

ASSESSMENT TOOLS	Baseline	3-month follow-up	8-month follow-up
*Demographic information*	✓	✓	✓
*General Health questionnaire*	✓	✓	✓
*Self-Reporting Questionnaire*	✓	✓	✓
*Social Participation Scale*	✓	✓	✓
*EURO-5D Quality of Life*	✓	✓	✓
*WHO-Disability scale*	✓	✓	✓
*General Anxiety Disorder Scale*	✓	✓	✓
*Patient Health Questionnaire*	✓	✓	✓
*Client Satisfaction Questionnaire (only in intervention condition)*	–	–	✓
*Economic Questionnaire*	✓	✓	✓

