### Sample size and power calculations

A trained lay health worker-led intervention study conducted in India reported a risk difference of 12% at follow up between intervention and control condition for the recovery of CMD patients [5, 37]. The sample size for this SW-CRCT is calculated to detect a 13% difference in CMD cases at a 3-month follow-up using GHQ-12 as a categorical measure between the intervention (58% improved) and control condition (45% improved). Assuming an intra-cluster correlation coefficient of ICC = 0.1, number of steps (t = 4), number of clusters randomized in each step (k = 14), average cluster size (m = 4), power (80%) and alpha of 0.05, a sample size of 1120 participants is needed, with approximately 56 individuals per cluster per period (Fig. 1, 3). The sample size was calculated using the “stepped wedge” function of STATA version 14 [38].

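### The primary outcome is stated inconsistently: one time point in the Abstract, two time points on two unranked scales in the Methods, and only the categorical 3-month measure in the sample size

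*Protocol article*

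**What the plan says.** All references are to the protocol article.

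- **Abstract, Methods:** "The primary outcome is symptomatic improvement measured through the GHQ-12 at a 3-month follow-up". One time point is given and the scale is not named.
- **Primary outcome:** improvement is measured "from baseline to 3-month and 8-month follow-up to evaluate sustained effects of the intervention". The section then says "GHQ-12 scores will be analyzed as both continuous (ranging from 0 to 12) and categorical outcomes", with a case defined as a score of 3 or more and a non-case as a score below 3. Neither scale is put first.
- **Sample size and power calculations:** the trial is sized to "detect a 13% difference in CMD cases at a 3-month follow-up using GHQ-12 as a categorical measure", with 58% improved under the intervention and 45% under control, "intra-cluster correlation coefficient of ICC = 0.1", 80% power and alpha 0.05. The result is 1,120 participants.
- **Statistical analysis:** a mean difference is planned for continuous outcomes and an odds ratio for categorical ones, with 95% confidence intervals. No analysis of the GHQ-12 is named as the principal one.
- **Secondary outcomes:** "Secondary outcome measures are assessed at 3 and 8 months after the start of the intervention". The Primary outcome section counts from baseline instead.
- **Design:** each period lasts 5 months, chosen to fit the baseline and 3-month data collection.

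**The concern.** A confirmatory trial needs one primary endpoint, or a stated rule for combining several. Here two time points and two scales stand under the primary label, which makes four candidate analyses, and only one of them is the basis of the sample size. If the results differ by scale or time point, nothing in this document settles which one answers the trial's question. The choice could then be made after the results are known, and the 5% error rate used for planning would no longer describe the claim.

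The 8-month results have a further weakness. Follow-up of 8 months is longer than the 5-month period, so some controls are assessed after their own villages have started the intervention.

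**Working it through.** **1. The plan's own figure.** I used the Hussey–Hughes variance for a cross-sectional stepped wedge. Inputs from the sample-size section: 4 steps, 14 clusters per step, 4 participants per cluster-period, ICC 0.1, 58% against 45%. My assumptions: one baseline period before the 4 steps, a two-sided test, and ICC as a share of total variance.

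- I = 4 × 14 = 56 clusters, T = 5 periods, N = 56 × 5 × 4 = 1,120. This matches the plan.
- Total variance at the mean proportion 0.515: 0.515 × 0.485 = 0.2498. Between clusters: τ² = 0.1 × 0.2498 = 0.02498. Variance of a cluster-period mean within cluster: σ² = 0.9 × 0.2498 / 4 = 0.05620.
- Treated cluster-periods: U = 140. Sum of squared column totals: W = 0 + 14² + 28² + 42² + 56² = 5,880. Sum of squared row totals: V = 14 × (16 + 9 + 4 + 1) = 420.
- Var = I σ²(σ² + Tτ²) / [(IU − W)σ² + (U² + ITU − TW − IV)τ²]
- Numerator: 56 × 0.05620 × 0.18109 = 0.5699. Denominator: 1,960 × 0.05620 + 5,880 × 0.02498 = 257.0. SE = √0.002217 = 0.0471.
- Power = Φ(0.13 / 0.0471 − 1.96) = 78.8%. Using the control-rate variance gives 79.2%, and the average of the two binomial variances gives 79.5%.

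So 1,120 reproduces to within about 1 point of the stated 80%, for one test: categorical GHQ-12 at 3 months.

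**2. Counting the candidates.** 2 time points × 2 scales = 4 analyses. One is powered. Two of the four are at 8 months.

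**3. False-positive rate if any one success counts.** The document gives no correlations. I assumed 0.7–0.8 between scales and 0.3–0.7 between time points, took the four test statistics as normal with the product of those correlations, and simulated P(any |z| > 1.96).

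| Analyses treated as primary | Assumed correlations | P(at least one false positive) |
|---|---|---|
| 3-month categorical only | – | 5% |
| Both scales at 3 months | scales 0.7–0.8 | 7.8–8.3% |
| All four | scales 0.7–0.8, times 0.3–0.7 | 12.8–15.6% |
| All four, wider range | scales 0.5–0.9, times 0.3–0.7 | 11.6–16.9% |
| All four, independent (bound for reference) | 0 | 1 − 0.95⁴ = 18.5% |

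**4. Cost of keeping all four as primary.** With a Bonferroni split (0.05 / 4 = 0.0125), the planned test at 1,120 participants has about 60–61% power. Restoring 80% needs about 6.15 participants per cluster-period, or 56 × 5 × 6.15 = 1,722.

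**5. Crossover before 8 months.** In the layout that yields 1,120, the four groups spend 1, 2, 3 and 4 periods in control, which is 10 control group-periods. Each group has one last control period, so 4 of 10 are of this kind. The group switches at most 5 months after recruitment in that period, so the 8-month visit falls after the switch. With 56 recruited in each group-period, that is about 40% of controls. The 3-month visit fits inside the 5-month period as the Design section intends.

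**The case against.** The strongest reply is that the article does point to a principal endpoint. The Abstract names 3 months alone, the sample size uses 3 months on the categorical scale alone, and the period length was set around 3-month follow-up. The Primary outcome section gives 8 months its own purpose, sustained effects, which can be read as supportive. This has force. It is why the higher error range is an upper scenario and about 8% is the figure if 8 months is only supportive. It does not remove the problem: 8 months still stands in the sentence that defines the primary outcome, and the two scales at 3 months remain unranked.

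A reader might infer more than the text supports:

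- **Four primary tests at 5% each, any one making the trial positive.** The article never counts its tests and states no success rule, and alpha 0.05 appears only in the sample size. If success were required on both scales, the error would be below 5%.
- **A missing alpha split or testing order as a fault in itself.** Those commonly sit in a statistical analysis plan, which is not shown. The identity of the primary endpoint is a protocol matter, and here it is stated in two ways.
- **Every 8-month comparison spoiled by crossover.** Only controls whose group switches before their 8-month visit are affected.
- **A rival primary endpoint created by the two clocks.** Counting from the start of the intervention appears only in the sentence on secondary outcomes. Table 1 uses a baseline column for nearly every tool. It is loose wording, worth correcting because controls have no intervention start.

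**Conclusion.** The point holds as an inconsistency in the definition of the primary outcome between the Abstract, the Primary outcome section and the sample size. The sample size itself is sound for the one endpoint that it covers.

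The size of the problem is conditional. Under an any-one-suffices rule the error is about 8% with both scales at 3 months, and up to about 13–16% with both 8-month analyses added. Both figures rest on my assumed correlations and on a rule that the document does not state. What does not depend on those assumptions is that the text, as it stands, lets the headline result be chosen from more than one analysis, two of which include controls assessed after crossover.

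**What to change.** 1. State one primary outcome in the Abstract, the Primary outcome section and the sample-size section: GHQ-12 below 3 (non-case) at 3 months after the baseline interview, in both conditions. All participants enter with a score of 3 or more, so this is the improvement that the sample size describes.
2. Make the continuous GHQ-12 at 3 months and both 8-month GHQ-12 analyses secondary.
3. Reword the opening of the Secondary outcomes section so that follow-up is counted from the baseline interview in both conditions.
4. Record and date the change before outcome data are analysed by condition. The Trial status section gives August 2019 as the end of recruitment, so the record should also say that no outcome comparison informed the choice. Check that the registry entry, which I have not seen, agrees.

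The planned 1,120 participants, the power of about 79–80% and the data collection stay as they are. The downside is small: a late, dated clarification of the primary outcome, which readers will want to see justified.

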### Secondary outcomes

Secondary outcome measures are assessed at 3 and 8 months after the start of the intervention (Table 1).

**Table 1 Tab1:** Follow-up assessment of tools with time points

ASSESSMENT TOOLS	Baseline	3-month follow-up	8-month follow-up
*Demographic information*	✓	✓	✓
*General Health questionnaire*	✓	✓	✓
*Self-Reporting Questionnaire*	✓	✓	✓
*Social Participation Scale*	✓	✓	✓
*EURO-5D Quality of Life*	✓	✓	✓
*WHO-Disability scale*	✓	✓	✓
*General Anxiety Disorder Scale*	✓	✓	✓
*Patient Health Questionnaire*	✓	✓	✓
*Client Satisfaction Questionnaire (only in intervention condition)*	–	–	✓
*Economic Questionnaire*	✓	✓	✓

#### Quality of life

Improvement in quality of life among persons with CMD is assessed using a validated Gujarati version of EURO Quality of life- 5D (EQ-5D) [20]. The EQ-5D’s descriptive system is a preference-based Health Related Quality of Life measure with one question for each of the five dimensions that include mobility, self-care, usual activities, pain/discomfort, and anxiety/depression measured at 5 levels: no problems, slight problems, moderate problems, severe problems, and extreme problems. A lower score indicates a better quality of life [20].

#### Psychiatric symptoms

Improvement in psychiatric symptoms is assessed using a validated Gujarati version of the Self Reporting Questionnaire (SRQ). SRQ is a scale developed by the World Health Organization to screen for psychiatric disturbances for low- and middle-income countries. It consists of 20 questions which are scored 1 = yes and 0 = no, indicating the presence or absence of a particular symptom over the past month. SRQ is a continuous scale and responses are calculated as a total score ranging from 0 to 20, with lower scores indicating recovery of symptoms [21].

#### Disability

Reduction of disability and reduction in a number of days unable to work and improvement in productivity is assessed using a validated Gujarati version of the World Health Organization’s Disability Assessment Scale (WHO-DAS-12). The WHO-DAS-12 assesses overall functioning, in relation to difficulties due to health conditions. The scale has 12 items, with a 5-point rating scale ranging from none, mild, moderate to severe and extreme. Responses are calculated as a total score ranging from 12 to 60 [22].

#### Depression and anxiety symptoms

Improvements in depression symptoms are assessed using a validated Gujarati version of the Patient Health Questionnaire (PHQ-9). PHQ-9 scores range from 0 to 27, with a higher score indicating more severe symptoms [23]. Improvements in anxiety scores are assessed by using a validated Gujarati version of Generalized Anxiety Disorder (GAD-7) with total scores ranging from 0 to 21 [24].

#### Social Participation

Increases in social participation is assessed using the Social Participation Scale (SPS) [25]. The SPS is an 18-item interview-based instrument measuring perceived problems in major domains of life such as learning and applying knowledge, communication, mobility, self-care, domestic life, interpersonal interactions, major life areas (like work, life, and employment) and community (like leisure, recreation, political life). The scale allows quantification of participation restrictions experienced by people affected by disability or other stigmatized conditions. The 18 items are rated on a 5-point scale ranging from 0 (no problem) to 5 (large problem). Responses are calculated as a total score ranging from 0 to 90 [26].

#### Service User Satisfaction

User-satisfaction with the intervention is assessed using a validated Gujarati version of the Client Satisfaction Questionnaire (CSQ) [25] at 8-month follow-up. The CSQ is an 8-item scale assessing client satisfaction with care/treatment received. The scoring uses a 4-point rating scale and is scored by summing the individual scores to produce a range of 8 to 32, with higher scores indicating greater satisfaction with care [27].

#### Specificity of identification of CMD cases

The accuracy of Champions identifying community members with CMD by Champions is assessed using the GHQ-12.

### Economic Evaluation

The most common measure of efficiency of interventions in the health sector is cost-effectiveness analysis (CEA) which measures health-related benefits and expresses these in a natural unit such as lives saved, or symptoms reduced. A return-on-investment analysis, however, expresses benefits in monetary terms relative to investments made. Expressing both the costs and the full range of benefits of an intervention in the same units (money) has the distinct advantage of making investment decisions very straightforward [28]. If the money value of the benefits of an intervention is larger than the cost of the intervention, it may be regarded as a sound investment. Hence, we have chosen to do ROI analysis for the *Atmiyata* intervention.

Costs are calculated using both government and societal perspective [29]. Perspective determines the cost components to be included in any cost analysis and societal perspective is the broadest viewpoint that covers all costs irrespective of who incurs these costs. On the other hand, a government perspective only includes costs incurred by the government for a particular health intervention. Costs are accounted under two categories: 1. total cost of the intervention and; 2. treatment cost of CMDs. Treatment costs are categorized as: direct medical cost, direct non-medical cost, and indirect costs. Direct medical costs include out of pocket expenses incurred in order to seek treatment (e.g. diagnostic tests, fees for consultation in clinics, traditional healers, hospitals, bed day charges at a public or private health facility). Direct non-medical costs include the amount spent for travelling to the health facility for the patient and accompanied persons for treatment, the amount spent on meal/food taken while waiting for treatment, expenses for overnight accommodation for seeking care, etc. Indirect costs represent the opportunity cost for the patient and their household members’ time related to CMD. Cost data is collected at baseline, 3 months and 8 months from all study participants. Time spent by the champion will be obtained from the program implementation data. The minimum wage rate of Gujarat will be used to value their time. Total hours spent on the program will be multiplied by hourly wage (obtained from the minimum wage rate) to get the time cost of the Champions. Benefits are considered in terms of improved health, functioning, participation, productivity, increased saving and investment, reduced informal care giving and health and welfare services. Lost workdays before and after the intervention will be obtained through the WHO-DAS 12 questionnaire and will be linked to the minimum wage rate to estimate the aggregate effect. Being alive and healthy is also considered valuable and the overall value of a life year can be broken down into its economic (instrumental) and health (intrinsic) elements. Following the approach used in prior ROI analyses in mental health, we use the figure of 0.5 times the per-capita income of India as the value of a healthy life year [28, 30, 31].

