### Economic evaluation analysis

All data will be analysed in Microsoft excel. The ratio of costs and benefits will be calculated and will be presented as an ROI. This will inform whether *Atmiyata* intervention is a sound investment. Apart from this, the study will also provide information on the economic burden of CMD in the Mehsana district, which is of value to funders, policymakers and can be used for advocacy purposes. The economic burden of CMD will include direct medical cost (out of pocket expenses on drugs, diagnostics, consultations fees during outpatient visits and hospitalization), direct non-medical cost (out of pocket expenses on transport, food, accommodation while seeking treatment) and indirect cost (time spent by a patient and accompanied persons). As one of the secondary outcomes of the study is to understand the changes in the quality of life of the CMD patient using the EQ-5D, we will conduct a cost-utility analysis as an additional analysis in the economic evaluation. Cost-utility analysis expresses the value for money in terms of a multi-dimensional health outcome. The incremental cost-effectiveness ratio, in this case, is usually expressed as the incremental cost to gain an extra quality-adjusted life-year (QALY) [29]. Consolidated Health Economic Evaluation Reporting Standards (CHEERS) checklist will be followed while reporting the results of ROI and cost-utility analysis [42].

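### The workday benefit in the return-on-investment analysis is a before–after change with no stated control contrast, so improvement expected under enhanced usual care is credited to the programme

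*Protocol article*

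**What the plan says.** The Economic Evaluation section lists the gains to be monetised: "Benefits are considered in terms of improved health, functioning, participation, productivity, increased saving and investment, reduced informal care giving", together with health and welfare services. For lost work it gives the instrument, the price and the comparison: "Lost workdays before and after the intervention will be obtained through the WHO-DAS 12 questionnaire and will be linked to the minimum wage rate". It also values a healthy life year at half of per-capita income, without saying what that gain is measured against.

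The Economic evaluation analysis section then says: "The ratio of costs and benefits will be calculated and will be presented as an ROI". Incremental language appears there only for the additional cost-utility analysis, whose result is "usually expressed as the incremental cost to gain an extra quality-adjusted life-year (QALY".

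The rule for judging an investment is in Economic Evaluation: "If the money value of the benefits of an intervention is larger than the cost of the intervention, it may be regarded as a sound" one.

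Other sections bear on this:
- Economic Evaluation: "Cost data is collected at baseline, 3 months and 8 months from all study participants".
- Disability, on the WHO-DAS-12: "Reduction of disability and reduction in a number of days unable to work and improvement in productivity is assessed". Table 1 schedules this scale at baseline, 3 and 8 months, and restricts only the satisfaction questionnaire to the intervention condition.
- Statistical analysis: primary and secondary outcomes are compared between conditions in a mixed model with period and intervention as fixed effects, cluster as a random effect, and baseline covariates. The section does not mention the ROI.
- Sample size and power calculations: planning rates at 3 months of 58% improved with the intervention, and for the "control condition (45% improved").

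**The concern.** A return on an investment is what the investment adds. A before–after change also contains whatever would have happened anyway, and the article itself expects a good deal of that, with almost half of controls improved by 3 months. Participants enter because they score 3 or more on the GHQ-12, so some improvement on re-measurement is likely, and lost workdays would fall with it to the extent that they follow symptoms. The Discussion adds that Champions may pick out people with higher GHQ scores. That could make this effect larger among intervention participants than among controls.

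At stake is whether benefits exceed costs, the test the article uses for a sound investment. A before–after numerator could show a gain from a programme with no effect. The primary clinical outcome is not affected.

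**Working it through.** **Inputs.** All come from Sample size and power calculations: improvement at 3 months p1 = 0.58 (intervention) and p0 = 0.45 (control), difference 0.13; 4 steps, 14 clusters per step, 4 participants per cluster-period, ICC 0.1, alpha 0.05 (taken as two-sided), total 1120. The article states no workday or ROI figure.

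**Step 1: reproduce the plan's figure, to confirm that the rates are the ones it was built on.**
- Periods: 1120 / (4 groups × 56 per group-period) = 5. Total: 14 × 4 × 5 × 4 = 1120, as stated.
- Power from the Hussey–Hughes variance, with I = 56 clusters, T = 5, U = 140, W = 5880, V = 420. Mean rate (0.45 + 0.58)/2 = 0.515, so total variance = 0.515 × 0.485 = 0.2498. Between-cluster τ² = 0.1 × 0.2498 = 0.02498. Cluster-period σ² = 0.9 × 0.2498 / 4 = 0.0562.
- Var = Iσ²(σ² + Tτ²) / [(IU − W)σ² + (U² + ITU − TW − IV)τ²] = 56 × 0.0562 × 0.1811 / (1960 × 0.0562 + 5880 × 0.02498) = 0.5699 / 257.0 = 0.00222, so SE = 0.0471.
- 0.13 / 0.0471 − 1.96 = 0.80, which gives power 0.788. Other choices of total variance give 0.792 and 0.795. This agrees with the stated 80%.

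**Step 2: what each contrast credits.** Assume that regained workdays are proportional to the share improved.
- Before–after: p1 = 58 improved per 100 treated.
- Beyond control: p1 − p0 = 58 − 45 = 13 per 100.
- Overstatement: 58 / 13 = 4.46. Share of the credit also expected under control: 45 / 58 = 77.6%.
- With a true effect of zero and the same control rate, before–after would still credit 45 per 100, when the attributable number is 0.

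**Step 3: effect on a benefit-to-cost ratio for the workday component.** Attributable ratio = before–after ratio × 13/58.
- 2.0 becomes 0.45; 4.0 becomes 0.90.
- Break-even needs a before–after ratio of about 4.46.

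**Step 4: sensitivity.** With the 13-point effect held, overstatement = (p0 + 0.13) / 0.13.

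| Control improvement | Overstatement |
|---|---|
| 10% | 1.8 |
| 20% | 2.5 |
| 30% | 3.3 |
| 45% | 4.5 |
| 50% | 4.8 |

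**Step 5: what the controls can support.** On a standard layout of four groups and five periods, the last period contains no controls. The control group-periods number 1 + 2 + 3 + 4 = 10, and 4 of these immediately precede a group's crossover. Periods last 5 months, so a control enrolled even at the start of such a period reaches the 8-month visit 8 − 5 = 3 months after the cluster has switched. The 3-month visit is meant to fall within the period.

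**The case against.** The strongest reply is that the sentence names an instrument and a price, not an estimator. Every cluster starts in control and crosses over, and each period samples different people, so the time before the intervention could mean the control condition. The text does not say this, and a comparison of lost workdays around an intervention reads most naturally as a within-person change. The other reading would not rescue the sentence. An unadjusted comparison across the wedge mixes the effect with secular trend and with the switch from electoral-roll to Champion-list recruitment.

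A second reply is that the controlled analysis already exists. Days unable to work belong to a secondary outcome, Statistical analysis covers secondary outcomes, and a condensed article may leave the link to the ROI to a fuller document. It stands that no new model is needed, and it would be wrong to infer that the trial has no controlled estimate of lost workdays. But the point does not rest on an omission: for the one benefit whose comparison is stated, that comparison is before–after, while incremental wording is kept for a different analysis.

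Three further objections stand in full:
- The 45% and 58% are GHQ-12 planning rates, and workdays are one benefit among several. A reader might infer that the whole ROI is overstated 4.5-fold. The article supports no such figure.
- Entry is on the GHQ-12, not on lost workdays, so a fall in lost workdays without the programme is likely rather than certain.
- A reader might infer that concurrent controls are available throughout and that subtracting them removes the bias. Step 5 shows the first is untrue on a standard layout. On the second, the Discussion concedes that the different recruitment routes may confound the effect.

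**Conclusion.** The point holds for the workday component. As written, the plan values it by a before–after change and so credits the programme with improvement that would occur under enhanced usual care. The direction of the error rests on the plan's own expectation of improvement among controls, provided that workdays respond at all to symptoms.

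Its size is an illustration: about 4.5-fold on the planning rates, and 1.8- to 4.8-fold for control improvement of 10% to 50% with the 13-point effect held. Both figures assume that regained workdays are proportional to GHQ-12 improvement. For the healthy life year and the other benefits, the article does not say which contrast is used. They may or may not share the fault, and no factor can be put on the ROI as a whole. Nor does the ROI settle the investment question by itself; the article presents it as informing that judgement.

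**What to change.** In Economic Evaluation, replace the before–after wording with something like this: *Lost workdays averted will be estimated as the intervention-minus-control mean difference in WHO-DAS-12 lost workdays, from the mixed model in Statistical analysis (period as a fixed effect, cluster as a random effect, baseline lost workdays as a covariate). This difference will be priced at the minimum wage, and its confidence interval will be carried into the ROI. The other monetised benefits will use the same control-adjusted contrast.* Add a cross-reference in Economic evaluation analysis.

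No new data are needed, because the WHO-DAS-12 and the economic questionnaire are scheduled in both conditions. The costs are:
- The ROI will probably be less favourable, and less precise, because a difference between conditions carries the sampling error of both.
- The 8-month contrast is limited, since some controls' clusters will have crossed over by then. The 3-month contrast is cleaner, and the report should say which one feeds the ROI.
- Baseline adjustment may not remove the confounding from electoral-roll versus Champion-list recruitment, so that limitation should accompany the ROI.
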